#### Confidence in trial arm

Due to the unblinded nature of the trial, participants are asked prior to randomisation to rate their confidence of each treatment arm being successful. This is measured again at +4 and +12 weeks. We will be able to determine whether expectation of success in the treatment they were allocated is associated with attrition rates.

### Sample Size

Acceptability and feasibility is measured qualitatively through interviews and by measurement of recruitment and attendance rates. These outcomes are descriptive and not analysed using statistical tests and so a power calculation for them would be inappropriate.

The secondary aim is to identify whether dietary interventions affect cravings for cigarettes. In the trial by Danielsson [25] the difference in cravings for cigarettes at week 2 was mean 1.6 in the control and mean 1.1 in the VLCD group with a standard deviation of 0.7. The control in the Danielsson trial was a standard (not individualised) 1600 kcal diet, a moderate energy restriction, likely to lead to increased hunger. We are looking to detect a difference of the same magnitude between our hungry (IDAP) and not hungry (control) or hunger suppressed (VLCD) groups. Using Epicalc with 80% power and a type 1 error rate of 5% we need 30 participants in each group and 90 in total to detect a significant difference between them. For sufficient power to detect a difference in an abstinent subgroup, assuming a 60% abstinent rate in the first few weeks, we are aiming to recruit 42 in each group.

Such a trial would be large enough to differentiate between dietary changes that reflect a poor to a healthy diet using a dietary index, this is based on the figures by Freisling et al in 2009 [38] who validated a food frequency index using values of <32 and >39 for a poor and very good diet respectively. With a standard deviation of 5.7, 10 people would be needed in each arm to detect a difference.

Running a larger trial to identify long term effects on abstinence and weight is premature at this stage, although we are carrying out all the measurements that would be needed in such a trial to assess feasibility.

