**Methods:**

This is a 3 armed, unblinded, randomized controlled trial in overweight (BMI > 25 kg/m^2^), daily smokers (CO > 10 ppm); with at least 30 participants in each group. Each group receives identical behavioural support and NRT patches (25 mg(8 weeks),15 mg(2 weeks),10 mg(2 weeks)). The VLCD group receive a 429-559 kcal/day liquid formula beginning 1 week before quitting and continuing for 4 weeks afterwards. The modest energy restricted group (termed individual dietary and activity planning(IDAP)) engage in goal-setting and receive an energy prescription based on individual basal metabolic rate(BMR) aiming for daily reduction of 600 kcal. The control group receive usual dietary advice that accompanies smoking cessation i.e. avoiding feeling hungry but eating healthy snacks. After this, the VLCD participants receive IDAP to provide support for changing eating habits in the longer term; the IDAP group continues receiving this support. The control group receive IDAP 8 weeks after quitting. This allows us to compare IDAP following a successful quit attempt with dieting concurrently during quitting. It also aims to prevent attrition in the unblinded, control group by meeting their need for weight management. Follow-up occurs at 6 and 12 months.

Outcome measures include participant acceptability, measured qualitatively by semi-structured interviewing and quantitatively by recruitment and attrition rates. Feasibility of running the trial within primary care is measured by interview and questionnaire of the treatment providers. Adherence to the VLCD is verified by the presence of urinary ketones measured weekly. Daily urges to smoke, hunger and withdrawal are measured using the Mood and Physical Symptoms Scale-Combined (MPSS-C) and a Hunger Craving Score (HCS). 24 hour, 7 day point prevalence and 4-week prolonged abstinence (Russell Standard) is confirmed by CO < 10 ppm. Weight, waist and hip circumference and percentage body fat are measured at each visit.

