### Analysis and Statistical Methods

Semi-structured interview and focus group transcripts will be coded according to content and common themes regarding acceptability and feasibility will be identified.

Quantitative measures of acceptability will be presented as descriptive statistics.

The outcomes between the three arms of the study will be compared using statistical tests on adequately powered measures. Descriptive statistics (mean, SD and 95% CI) will be presented on underpowered measures.

Multilevel modelling based on the Piasecki model of cigarette withdrawal [33] will be used to investigate the effects of the dietary interventions on urges to smoke during the first 4 weeks of quitting. We will investigate whether these effects are mediated by hunger/food craving score (HCS) and ketosis. We will adjust for confounding variables e.g. active treatment for depression. Analysis will be carried out on all those who continued to try to quit regardless of lapses to smoking and this will be adjusted for in the model as described above.

Significance is set at the 5% level, exact p values will be given and 95% confidence intervals where appropriate.

Analysis of data from treatment stage 1 will be undertaken once every participant has completed this stage. Analysis from treatment stage 2 and follow-up at 6 months and one year will be undertaken once participants have gone through each of these phases.

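### Recruiting 42 per group leaves about 25 abstinent participants per arm at the assumed 60% abstinence, not the 30 the plan says it needs, so power in that subgroup is about 70%

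*Protocol article*

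**What the plan says.** The Sample Size section of the protocol article sizes the trial on its secondary aim, urges to smoke. It takes the planning values from an earlier VLCD trial, "mean 1.6 in the control and mean 1.1 in the VLCD group with a standard deviation of 0.7", and looks for a difference of that magnitude between arms. The resulting requirement is: "Using Epicalc with 80% power and a type 1 error rate of 5% we need 30 participants in each group and 90 in total".

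The next sentence extends the claim to participants who are abstinent. It seeks sufficient power in that subgroup and, "assuming a 60% abstinent rate in the first few weeks, we are aiming to recruit 42 in each group". No separate effect size, power or sample size is given for the subgroup. The Abstract states the minimum only, "with at least 30 participants in each group", which is compatible with an aim of 42.

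The Analysis and Statistical Methods section fits a multilevel model of urges over the first four weeks in everyone who keeps trying to quit, whether or not they lapse, with adjustment for lapses. It compares arms with statistical tests on adequately powered measures and presents descriptive statistics on underpowered ones. It adds: "Significance is set at the 5% level, exact p values will be given and 95% confidence intervals where appropriate".

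**The concern.** The abstinent subgroup is the only reason the plan gives for raising the target from 30 to 42. If 60% of an arm is abstinent, the subgroup is smaller than the number the preceding sentence calls necessary, so the stated target does not serve its stated purpose.

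What is at stake is how a subgroup result is read. A reader who relies on the sample-size statement would take a null comparison among abstainers as coming from an adequately powered analysis and might conclude that diet does not affect urges in people who have stopped smoking. The Background says the trial is meant to inform a larger study, so a wrong power statement could also be carried into that design.

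**Working it through.** **Inputs, all from the Sample Size section.** Means 1.6 and 1.1, so the difference is 0.5; SD 0.7; power 80%; type 1 error 5%; 30 per group required; 60% abstinent; 42 per group to be recruited. Sidedness is not stated. Two-sided is assumed, because it comes close to the stated 30 and fits the 95% confidence intervals in the analysis section.

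**1. Reproduce the 30.** Standardised difference d = 0.5/0.7 = 0.714.

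n = 2(1.960 + 0.842)²/d² = 2 × 7.85/0.510 = 30.8, so 31 per group. The t test gives 31.8, so 32. The stated 30 is thus reproduced to within two participants. Power at exactly 30 is 79% (normal approximation) or 78% (t test).

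**2. Try to reproduce the 42.**
- Dividing by the expected fraction: 30/0.60 = 50 per group. This does not give 42.
- Multiplying by one plus the expected loss: 30 × 1.40 = 42. This matches exactly, which suggests, but does not prove, that the 40% was added instead of divided out.

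**3. Abstinent participants expected from 42.** 42 × 0.60 = 25.2 per arm. For 42 recruits to leave 30 abstinent, abstinence would have to be 30/42 = 71.4%.

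**4. Power in the subgroup.** Normal approximation: power = Φ(0.5/(0.7√(2/n)) − 1.960). At n = 25.2, 0.7√(2/25.2) = 0.197 and 0.5/0.197 = 2.536, so power = Φ(0.576) = 0.718.

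| Evaluable per arm | Normal approximation | t test |
|---|---|---|
| 25 | 71.4% | 69.7% |
| 25.2 | 71.8% | 70.0% |
| 30 | 79.0% | 77.6% |
| 34 | 83.8% | 82.7% |
| 36 | 85.8% | 84.8% |
| 42 | 90.5% | 89.9% |

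**5. Detectable difference in the subgroup at 80% power.** Normal approximation: (1.960 + 0.842) × 0.197 = 0.55. The t test gives 0.57 at 25 per arm and 0.56 at 25.2, against the planned 0.50.

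**6. One-sided variant.** With one-sided 5%, n = 2(1.645 + 0.842)²/0.510 = 24.2, so 25 per group, and 25/0.60 = 41.7, which rounds up to 42. Power at 25 would be 81%. But this makes the base requirement 25, not the 30 that the plan states.

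**The case against.** The strongest reply is that little depends on this figure. This is a feasibility trial. Its primary objective is feasibility and acceptability, for which the plan rightly says a power calculation would be inappropriate. Urges to smoke are a secondary objective, and the section on measuring urges explains why the authors do not restrict attention to abstainers. The specified model uses everyone still trying to quit, and the analysis section sets out no separate test in the abstinent. All of this stands, and it limits the weight of the point.

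A second reply is that the plan asks only for *sufficient* power in the subgroup and does not repeat 80%. That is true of the wording, but 80% is the only standard given, and nothing signals a lower one for the subgroup. The one-sided variant does not rescue the figure either, because it conflicts with the stated need for 30.

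Several stronger readings are tempting and are not supported:
- *The craving analysis as a whole is underpowered.* It is not on these figures: with all 42 per arm evaluable, pairwise power is about 90%.
- *The rule on adequately powered measures compels a descriptive-only subgroup analysis.* That rule speaks of measures, sets no threshold and does not mention subgroups. Treating the subgroup comparison as estimation is a recommendation.
- *The 10 per arm for the diet index is also wrong.* The plan gives open-ended cut-offs (below 32, above 39) and never states a difference of exactly 7. With SD 5.7, a difference of 7.15 already gives 2 × 7.85 × (5.7/7.15)² = 9.98, which rounds up to 10. Nor do the documents establish that the index is a different instrument from the HCI, or that the HCI's SD is unknown.

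**Conclusion.** The point holds for the abstinent-subgroup power claim and no further. At the plan's own 60% abstinence, 42 per group gives about 25 abstinent per arm against a stated need of 30. Power is about 70% where the only standard offered is 80%.

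This rests on a two-sided 5% test, a pairwise comparison of equal arms, the planning difference and SD holding among abstainers, and abstinence of 60% in each arm. The shortfall closes only if abstinence is about 71%.

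A reader might infer that the trial must recruit more people or that its main analysis of urges is compromised. Neither follows, since the main model does not depend on the abstinent subgroup. The gap between 30 and 31 or 32 in the base calculation is of rounding size and would not merit a comment alone. This is a figure to correct, at modest severity for a feasibility trial.

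**What to change.** Keep the target of 42 per group and restate what it delivers in the Sample Size section:
- In a subgroup with 60% abstinence, about 25 per arm and about 70% power for a difference of 0.5 (SD 0.7, two-sided 5%); the difference detectable with 80% power is about 0.56–0.57.
- In all those still trying to quit, up to about 90% power if all 42 per arm are evaluable, and about 83–85% if 34–36 are. The condition should be stated, because drop-out is expected and is itself an outcome.

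Say that any comparison within the abstinent subgroup is underpowered and will be reported as estimates with 95% confidence intervals, and keep the multilevel model in everyone who continues to try to quit as the main analysis of urges. Optionally, note that the base requirement is 31 (normal approximation) or 32 (t test), and that 30 gives 78–79% power.

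The cost is wording only. No one extra is recruited and the main analysis is unchanged; one stated power claim becomes less favourable. If the authors prefer to keep the subgroup claim as it stands, the target would have to be 50 per group, 150 in total instead of 126, to leave 30 abstinent per arm.

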### Randomisation

Randomisation is computer generated by an independent statistician within the Primary Care Clinical Research and Trials Unit (PCCRTU) using random permuted blocks of length 6, stratified by practice. The numbers are entered into the trial database by an independent computer programmer within the trials unit. The database conceals randomisation until after participants have been screened and entered into the trial. At week -3 the clinician clicks on the randomisation tab in the database and this reveals the arm to which the participant is allocated. The database is set up so that the randomisation 'tab' will not work until all data from week -2 has been completed. Therefore it is impossible for anyone to see treatment allocation beforehand. This greatly minimises any risk of the trial randomisation being undermined.

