## Methods

### Participants

Overweight (BMI > 25 Kg/m^2^) smokers listed on the databases of participating general practices are invited to take part by a letter from their General Practitioner (GP). All participants are from practices in Birmingham East and North Primary Care Trust (PCT) and Worcestershire PCT, in the UK. (See additional file 1 for substantial amendment to recruitment strategy).

Interested participants telephone the trial office at The University of Birmingham for further information; they provide verbal consent to initial telephone screening for eligibility. If considered eligible they are given an appointment with a trial nurse for full screening where they are invited to give informed consent for participation. The trial office sends the patient information sheet out so that it is received at least 24 hours before their first appointment. The clinics are run at local GP practices, daytime appointments are offered from 8.30 am until 7 pm.

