#### Training and supervision

Treatment is provided by trained practice nurses. Training is given by NHS stop smoking services (2 days), a research nurse and a general practitioner (GP) (1/2 day), and a registered dietitian (1.5 days). Nurses are given the clinical protocol to read before training sessions. Training includes explanation of dietetic and behavioural interventions and practicing the interventions on each other. The clinical protocol is clarified where needed and questions answered. The aim of the training is to equip the nurses so that, once they have completed it, they feel confident to deliver the interventions according to the clinical protocol.

After the training, 'hands on' supervision is available for the first few clinics. Immediate telephone access to the dietitian and GP is available for all clinical queries throughout the rest of the trial.

Medical history and any medication used or altered during the trial is monitored. Any significant changes in clinical condition of individual participants, as measured on a weekly basis, is discussed with the supervising GP and action taken, e.g. clinically significant fall in blood pressure in participants on the VLCD taking anti-hypertensives will require adjustment of anti-hypertensive medication. The participant's own GP is kept informed.

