### Assessment of safety

Potential participants' safety is ensured by screening for eligibility using a structured form completed by the trial healthcare professionals. This will record evidence of eligibility and that the person does not have any exclusion criteria. In addition, the nurse will take a general medical and drug history to assess for other complicating diseases. Any queries remaining as a result of this process are resolved by discussion between the trial nurse, chief investigator and the relevant physicians providing routine medical care, usually the participant's GP. Such concerns are unusual but not rare. Typically, they arise from a participant's hazy knowledge or understanding of their past medical history and are usually readily resolved. No blood or further medical testing is necessary to ensure safety.

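### A fixed block of 6 within each practice, in an open trial, lets practice staff deduce some upcoming allocations, so the claim that foreknowledge is impossible is too strong

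*Protocol article*

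**What the plan says.** The Randomisation section of the protocol article specifies "random permuted blocks of length 6, stratified by practice". An independent statistician generates the list and an independent programmer enters it. After that, "the clinician clicks on the randomisation tab in the database and this reveals the arm", and the tab stays locked until earlier data are complete. The section concludes: "Therefore it is impossible for anyone to see treatment allocation beforehand". The next sentence adds that this greatly reduces the risk of the randomisation being undermined.

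The surrounding facts are these:
- The abstract states: "This is a 3 armed, unblinded, randomized controlled trial".
- Under Participants, people telephone the trial office first. Then: "If considered eligible they are given an appointment with a trial nurse for full screening". Clinics take place at local practices.
- Under Training and supervision: "Treatment is provided by trained practice nurses".
- No allocation ratio is stated, but under Sample Size "we need 30 participants in each group and 90 in total", which points to 1:1:1 and so to two places per arm in each block.

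The article does not say that the block length varies or that it is withheld from those who enrol.

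**The concern.** Concealment has two parts: the list must not be visible, and the next entry must not be deducible from entries already revealed. The locked tab secures the first part only. In an open trial each allocation becomes known at the practice when it is issued. The stratum is that same practice, and the block length is constant. Someone who keeps count therefore needs no access to the list to know how some blocks must end.

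If upcoming arms can be foreseen, they may influence who is entered. Some entry criteria call for judgement, such as whether a person is willing and able to follow the intervention, or whether alcohol or drug misuse is suspected. Selective entry by arm would affect drop-out, attendance and adherence by arm, which are acceptability outcomes, and the secondary comparison of self-recorded urges to smoke. The trial is also described as a small-scale model of a larger one, so the scheme may be carried forward.

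**Working it through.** The article gives no figure for predictability, so there is none to reproduce.

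**Inputs.** Three arms, open (abstract). Fixed block of 6, one list per practice (Randomisation). Allocation 1:1:1, inferred from 3 × 30 = 90 (Sample Size), hence 2:2:2 per block.

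**Further assumptions.** The observer knows the block length and every earlier arm in the practice, and blocks are completed.

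**Number of orderings.** 6!/(2!·2!·2!) = 90, all equally likely.

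**Arm certain.**
- Position 6: always.
- Position 5: when the last two places hold the same arm, 3/C(6,2) = 3/15 = 20%.
- Positions 1-4: never.
- Mean: (0.2 + 1)/6 = 1.2/6 = 20%.

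**At least one arm excluded** (this includes the certain cases).
- Position 3: the first two are equal, 3/15 = 20%.
- Position 4: the first three are not all different, 1 − 8/C(6,3) = 1 − 8/20 = 60%.
- Positions 5 and 6: always.
- Mean: (0.2 + 0.6 + 1 + 1)/6 = 2.8/6 = 47%.

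**Best guess** (choose the arm with most places left).
- Position 1: 2/6 = 33%.
- Position 2: 2/5 = 40%.
- Position 3: 2/4 = 50%.
- Position 4: 0.6 × 2/3 + 0.4 × 1/3 = 53%.
- Position 5: 0.2 × 1 + 0.8 × 1/2 = 60%.
- Position 6: 100%.
- Mean: 3.37/6 = 56%, against 2/6 = 33% by chance.

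| Position | Certain | An arm excluded | Best guess right |
|---|---|---|---|
| 1 | 0% | 0% | 33% |
| 2 | 0% | 0% | 40% |
| 3 | 0% | 20% | 50% |
| 4 | 0% | 60% | 53% |
| 5 | 20% | 100% | 60% |
| 6 | 100% | 100% | 100% |
| Mean | 20% | 47% | 56% |

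Enumerating all 90 orderings by computer gives the same values.

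**Dependence on practice size.** Enrolment per practice is not given, so a range is needed.
- Two enrolled: no certain allocation, and no arm ever excluded.
- Four enrolled: no certain allocation; an arm excluded for (0 + 0 + 0.2 + 0.6)/4 = 20%.
- Multiples of six: the means in the table. If all 90 participants fell in completed blocks, 0.20 × 90 = 18 allocations would be certain. That is the upper end.

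**Varying block lengths.** This was simulated with 3,000 sequences of 24 participants per practice, each length equally likely. The observer knows the possible lengths but not which was drawn.

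| Block lengths | Certain | An arm excluded | Best guess right |
|---|---|---|---|
| Fixed 6 (check) | 20% | 46% | 56% |
| 6/9 | 5% | 13% | 53% |
| 3/6/9 | 3% | 9% | 55% |
| 6/9/12 | 2% | 7% | 52% |

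The fixed-6 row agrees with the exact result within simulation error.

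**The case against.** Several points on the other side stand.

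**Roles and knowledge are not documented.** A reader might infer that one nurse screens, randomises, treats and keeps the tally. The article speaks of a trial nurse, a clinician and practice nurses, and does not say they are the same person or that any one of them knows every earlier arm. It also does not say whether the clinical protocol given to nurses states the block length. Deduction requires both pieces of knowledge.

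**Eligibility is less open than it may look.** A reader might infer that relative contraindications to the very low calorie diet are a matter of discretion. Under Exclusion Criteria, absolute and relative contraindications alike exclude a person from the whole trial. Under Assessment of safety, "Any queries remaining as a result of this process are resolved by discussion between the trial nurse, chief investigator" is followed in the same sentence by the physicians giving routine care, so it describes a joint decision and works as a check at least as much as an opening. Judgement remains in other criteria, but only there.

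**Timing.** A reader might infer that a nurse could time first appointments to catch a favoured arm. Participants call the trial office and are given an appointment. Nothing says the nurse controls the order.

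**Wording.** The article says the allocation cannot be seen, which the lock supports, and then speaks of minimising risk, not of removing it. The contradiction is therefore partly one of words. Even so, a reader will take the sentence as a claim that nobody can know the next arm, and the mechanism does not deliver that.

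**Purpose.** The primary objective is feasibility, reported descriptively, and a fixed block is a defensible way to balance three arms within practices. This limits the consequence but does not restore concealment.

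**Conclusion.** The point holds in a limited form. A constant block of 6 per practice in an open trial makes some allocations deducible by staff who know or infer the block length and know the earlier arms. The locked tab does not prevent this, so *impossible* overstates the protection.

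The 20%, 47% and 56% are a ceiling. They rest on 1:1:1 allocation, completed blocks, a known block length and full knowledge of earlier arms. A reader might take them as the rate in this trial, but the documents do not support that, because the number and size of practices are not given. Small practices would show much less predictability or none beyond guessing. Nor is there any evidence that entry was selective. This is an avoidable risk of bias of unknown realised size, and it should be corrected because the remedy is cheap.

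**What to change.** For allocations not yet issued, the independent statistician should regenerate the list within practice with randomly varying block lengths in multiples of 3, for example 3/6/9 or 6/9/12, and withhold the lengths from practice staff. Under the simulation's assumptions, certain allocations fall from 20% to about 2-3% and cases with an excluded arm from 47% to about 7-9%. Best-guess success falls only to about 52-55%, so the change removes most of the certainty but not all of the predictability.

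The cost is one regenerated list and slightly more imbalance within small practices: an unfinished block of 9 or 12 can leave arms 3 or 4 apart, against 2 for a block of 6.

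In the Randomisation section, replace the claim of impossibility with a statement that the list cannot be viewed before a participant is entered. If recruitment has already closed, keep the list as it is and report the remaining predictability as a limitation, together with the number of participants per practice.
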